### Control Group

The control group will continue to work as normal with no changes in their routine or environment. They will complete the same measurements as the intervention group.

### Measurements

All measures for both intervention and control groups will be performed at baseline and during the final week of the 8-week study period. Questionnaires will be completed online using Qualtrics survey software (Qualtrics, Provo, Utah, USA) with physical measures taking place at participant's workplaces in a private room.

#### Primary Outcome Measure: Workplace Sitting Time

The primary outcome measure is sitting time at work, which will be measured using an activPAL3 activity monitor (PAL Technologies Ltd., Glasgow, UK). The activPAL is a portable lightweight device, which is usually worn on the front of the mid-thigh to take measurement of postural information by recognizing periods of lying down/sitting, standing, and stepping based on the inclination of the thigh (39, 40). The activPAL has high reliability and validity for assessing sitting, standing and stepping (41). In this study, the device will be worn on the right thigh for seven full consecutive days (42) at baseline and during the last week of the intervention. The device will be waterproofed by wrapping it within a nitrile sleeve and an adhesive medical dressing. In addition, participants will complete a diary to keep record of their waking time, working hours and time they go to bed while wearing the device to enable calculation of waking and working time wear periods (42). Data from the activPAL will be considered valid only if the device is worn for a minimum of 75% of the workplace monitoring time (39, 40). The sitting time at work variable will be normalized by expressing it as a percentage of the duration of the working day for each participant.

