## Introduction

Sedentary behavior has been described as any waking behavior in a sitting, reclining or lying posture that has an energy expenditure of ≤ 1.5 metabolic equivalents (METs) (1). In the United Kingdom, high levels of sedentary behavior have been reported with male and female employees sitting more than 11 h/day on average (2). Studies have identified the workplace as a major contributor to excessive sitting (3) with one study reporting that office workers spent 79% of their working day sitting and 42% of their work hours engaging in prolonged sitting (i.e., sitting bouts ≥ 30 min) (4).

Individuals who spend prolonged periods being sedentary have an increased risk of adverse health outcomes, including type 2 diabetes, cardiovascular disease, some cancers, and mental health problems such as depression and anxiety (5–9). This has led to incorporating a focus on reducing and breaking up sedentary behavior in national and international physical activity guidelines (10, 11). As high amounts of sitting are accumulated in the office workplace, this is a key setting where interventions could be implemented to improve occupational and public health. Indeed, an expert consensus statement recommended that workers who are in predominantly desk-based occupations should start by accumulating 2 h of standing and light activity during working hours each day, and progress to reaching a target of 4 h per day (12).

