There is a growing body of evidence that suggests height-adjustable workstations (i.e., a workstation that permits the user to interchangeably work in a seated or standing posture) could be effective for decreasing sitting in the workplace (13). When height-adjustable workstations are provided as part of multi-component interventions that also include strategies such as education, manager support, standing meetings, self-monitoring and social support, workplace sitting has been significantly reduced by 45 to 83 min/work shift after 12 months (14, 15). Although these interventions appear promising, management of organizations might be reluctant to implement them if productivity is negatively affected (16). With respect to productivity concerns, a systematic review reported that productivity is likely to be unaffected by using a height-adjustable workstation (17). There are also limited studies that have reported taking employee's perceptions and experiences into account when developing interventions to reduce workplace sitting (18), which may limit intervention adherence and effectiveness. By involving the target audience in the development of interventions, this will help to ensure their needs are met and enhance their adherence and engagement (19). The Behavior Change Wheel (BCW) (20, 21) has been recommended for guiding the systematic process of developing an intervention using a framework that takes into account the needs of the target audience. To the author's knowledge, only one previous office workplace intervention has been developed using the BCW (18); the SMArT Work intervention in National Health Service employees led to significant reductions in sitting at work and improvements in job performance, work engagement, occupational fatigue, sickness presenteeism, anxiety and quality of life over 12 months (15). Further research is required in other occupational groups to strengthen the evidence base for incorporating a focus on reducing and breaking up sitting in workplace policy and practice. Demonstrating the effectiveness of such interventions for improving work-related outcomes, such as worker productivity, will be important for encouraging the adoption of such changes in policy and practice. The use of ecological momentary assessment (EMA) facilitated through smartphone technology provides the opportunity to collect simultaneous time-stamped data with limited recall bias to elucidate on the temporal effects of posture and activities on work performance throughout the workday (22, 23). However, the effects of workplace sitting interventions on EMA measures of work-related outcomes is limited.

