#### Secondary Outcome Measures

##### Sitting, Standing and Stepping

In addition to workplace sitting, the activPAL will be used to measure total daily sitting time and the following variables for working hours and across the waking day: time spent in sitting bouts <30 min and ≥30 min, the number of sitting bouts <30 min and ≥30 min, standing time, number of sit-to-upright transitions, number steps and stepping time. Processing PAL (v1.1, University of Leicester, Leicester, UK) will be used to process the data. A validated algorithm (43) will be used to identify valid waking wear data with heat maps being generated to visually check classifications of waking wear time against information provided in the participant's diaries. Waking bout corrections will be made where errors are identified (42). A valid day for daily data will be accepted if wear time is ≥10 h per day; ≥500 steps per day and if not recording > 95% data in one activity category (i.e., sitting, standing or stepping). The resulting data for all primary and secondary activPAL outcome measures will be averaged across all valid days. All time variables for the working day will be normalized by expressing them as a percentage of the work shift duration. All count variables, such as the number of sitting bouts, will be normalized by expressing them as counts per hour.

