##### Adherence Analysis

Adherence to the intervention will be assessed using activPAL data for the working day. Participants will be classified into one of three groups at baseline and follow-up in line with recommendations from an expert statement on reducing sedentary time in the workplace (12): (1) meeting the recommended guidelines (MEETING) for standing and/or stepping at work of ≥4 h per work day, (2) meeting the minimal guidelines (MINIMAL) for standing and/or stepping at work of ≥2 h but <4 h per work day, or (3) sedentary (SED) i.e., not meeting MINIMAL or MEETING guidelines.

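### Working-day sitting is divided by the full shift although data are valid from 75% wear, so the primary percentage depends on how long the device was worn

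*Protocol article*

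**What the plan says.** Under Primary Outcome Measure: Workplace Sitting Time, the protocol article sets the denominator: "The sitting time at work variable will be normalized by expressing it as a percentage of the duration of the working day for each participant". Under Sitting, Standing and Stepping it repeats the rule for the related outcomes: "All time variables for the working day will be normalized by expressing them as a percentage of the work shift duration".

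The wear requirement is lower than full wear: "Data from the activPAL will be considered valid only if the device is worn for a minimum of 75% of the workplace monitoring time". On processing, the article states: "A validated algorithm (43) will be used to identify valid waking wear data", with a visual check against the diaries. The stated purpose of the diary is "to enable calculation of waking and working time wear periods". No sentence uses wear time as a denominator or rescales for non-wear.

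The Adherence Analysis classes use absolute hours upright. The top class, for example, is "meeting the recommended guidelines (MEETING) for standing and/or stepping at work of ≥4 h per work day".

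The models under Statistical Analysis contain arm, time and the baseline value, with participant and cluster as random effects. They contain no term for wear.

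**The concern.** The two parts of the ratio cover different time. The numerator appears to come from worn time only, while the denominator is the whole shift. A participant whose data count as valid may have up to a quarter of the shift in the denominator with nothing in the numerator. Sitting, standing and stepping then add up to the wear fraction and not to 100%.

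The primary outcome would then fall whenever wear falls. Three things are at stake:

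- **Bias.** If wear at follow-up differs between the arms, part of the wear difference is read as a difference in sitting. Participants are not blinded, so a difference in wear cannot be excluded by design.
- **Dilution.** If wear is equal but incomplete, the effect shrinks.
- **Noise.** If wear varies between participants, the spread of the outcome grows. The Sample Size section describes estimating the standard deviation as the main purpose of a pilot, so this matters even without bias. The baseline covariate carries the same error.

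The adherence classes share the problem, because recorded upright hours also shrink with wear.

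**Working it through.** The article gives no computed figure on this point, so there is nothing to reproduce. The check is direct arithmetic.

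**Inputs**

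- Sitting share s = 0.79, from the Introduction: "office workers spent 79% of their working day sitting".
- Background effects, also from the Introduction: "workplace sitting has been significantly reduced by 45 to 83 min/work shift after 12 months". They come from earlier interventions and are not a target of this trial.
- Wear fraction w from 0.75 to 1, from the validity rule.
- Shift length T = 480 min. This is an assumption: the article states no shift length, and 8 h matches the 9 am to 5 pm window for the momentary-assessment prompts. Results for 7 h and 9 h are given where they matter.
- Non-wear is excluded from the numerator, as the processing step implies.

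**One participant.** Recorded % = s × w.

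- At w = 0.75: 0.79 × 0.75 = 59.25%, which is 19.75 points too low.
- In minutes: 0.79 × 0.25 × 480 = 94.8 (83.0 at 7 h, 106.7 at 9 h).
- For scale: 45/480 = 9.4 points and 83/480 = 17.3 points.

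**Equal wear in both arms.** Recorded effect = true effect × w. At w = 0.75, 45 becomes 33.8 min and 83 becomes 62.2 min. This is the largest possible dilution, 25%.

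**Unequal wear.** Recorded contrast = (s_C × w_C − s_I × w_I) × T, with C for control and I for intervention. For a 5-point gap:

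| True effect (min) | w_C | w_I | Recorded (min) | Shift (min) |
|---|---|---|---|---|
| 45 | 0.95 | 1 | 26.0 | −19.0 |
| 45 | 1 | 0.95 | 61.7 | +16.7 |
| 83 | 0.95 | 1 | 64.0 | −19.0 |
| 83 | 1 | 0.95 | 97.8 | +14.8 |

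The bias is therefore about 15 to 19 min per 5 points, in either direction.

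**Mean wear gap needed to match the background effects.** Gap = effect/(s × T).

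- 8 h: 45/379.2 = 11.9 points; 83/379.2 = 21.9 points.
- 7 h: 13.6 and 25.0 points. 9 h: 10.5 and 19.5 points.

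**Noise.** As an illustration only, suppose wear is uniform between 75% and 100%. Its SD is 25/√12 = 7.2 points, which adds 0.79 × 7.2 = 5.7 points of spread to the outcome.

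**Adherence classes at the wear floor.** 4.0 h upright is recorded as 4.0 × 0.75 = 3.0 h, and 2.5 h as 1.9 h. Each drops one class.

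**With worn work time as denominator.** (0.79 × w)/w = 79% at every wear level, provided unworn work time resembles worn work time.

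**The case against.** The strongest reply is that the denominator sentences are condensed wording. The diary is said to serve the calculation of working-time wear periods, so the working day in the ratio may already mean worn working time. That is possible, but both denominator sentences name the day or the shift. If wear time was intended, both are misworded and need the same correction.

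Second, the direction is inferred. The article does not say how a removal inside working hours is handled. The device reads posture from thigh inclination, so a removed device left in the data might be scored as sitting, and the bias would then run the other way. This stands as a condition on the direction. It is also a reason to state the rule.

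Third, size. A reader might infer that the artefact can be expected to outweigh the intervention effect. The documents do not support that. The fall of almost 20 points is one participant averaging exactly the minimum wear, whereas 45 to 83 min are group means from 12-month studies. Between arms, equal wear cannot create an effect, and a mean gap of 12 to 22 points is unlikely: the device is waterproofed, held by an adhesive dressing and meant for seven full days, and both arms complete the same measurements. The 75% rule is an exclusion limit, not expected wear.

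A reader might also infer that waking-day times are left unnormalised. That rests only on the article's silence and is not part of this point.

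**Conclusion.** The point holds as a defect in the stated definition of the primary outcome. Followed as written, the rule makes the percentage depend on wear, and a better denominator is already available. The realistic consequences are moderate: dilution of at most 25%, added spread in a small pilot, and about 15 to 19 min of bias per 5-point wear gap between arms. The documents give no sign that wear will differ enough to create or cancel an effect of the cited size.

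This rests on four assumptions: non-wear is removed from the numerator; the shift is 8 h (7 and 9 h change the figures but not the conclusion); 79% is a fair sitting share; and the 75% floor applies to work time as a whole. The effect on the adherence classes is secondary, and the examples are again at the wear floor.

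**What to change.** - Define the primary outcome as worn work sitting time divided by worn work time.
- Use the same denominator for standing, stepping and sitting-bout times in the working day.
- State that non-wear is removed from both numerator and denominator.
- Report work-time wear by arm and visit.
- For the adherence classes, scale upright hours to the full shift before classifying (upright share of worn work time × shift length), at least as a sensitivity analysis.

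The cost is a change of wording and a small processing step, because wear must already be derived to apply the 75% rule. The small downside is the assumption that unworn work time resembles worn work time. It is milder than the present rule, which in effect assumes that none of the unworn time was spent sitting.

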#### Secondary Outcome Measures

##### Sitting, Standing and Stepping

In addition to workplace sitting, the activPAL will be used to measure total daily sitting time and the following variables for working hours and across the waking day: time spent in sitting bouts <30 min and ≥30 min, the number of sitting bouts <30 min and ≥30 min, standing time, number of sit-to-upright transitions, number steps and stepping time. Processing PAL (v1.1, University of Leicester, Leicester, UK) will be used to process the data. A validated algorithm (43) will be used to identify valid waking wear data with heat maps being generated to visually check classifications of waking wear time against information provided in the participant's diaries. Waking bout corrections will be made where errors are identified (42). A valid day for daily data will be accepted if wear time is ≥10 h per day; ≥500 steps per day and if not recording > 95% data in one activity category (i.e., sitting, standing or stepping). The resulting data for all primary and secondary activPAL outcome measures will be averaged across all valid days. All time variables for the working day will be normalized by expressing them as a percentage of the work shift duration. All count variables, such as the number of sitting bouts, will be normalized by expressing them as counts per hour.

##### Adherence Analysis

Adherence to the intervention will be assessed using activPAL data for the working day. Participants will be classified into one of three groups at baseline and follow-up in line with recommendations from an expert statement on reducing sedentary time in the workplace (12): (1) meeting the recommended guidelines (MEETING) for standing and/or stepping at work of ≥4 h per work day, (2) meeting the minimal guidelines (MINIMAL) for standing and/or stepping at work of ≥2 h but <4 h per work day, or (3) sedentary (SED) i.e., not meeting MINIMAL or MEETING guidelines.

##### Feasibility

Feasibility will be assessed based on recruitment response rate (percentage of people who express interest in participating in the study / number of invitations sent out to individuals x 100) and eligibility rate (percentage of individuals who are screened / number of individuals eligible to take part x 100). Retention rate will be calculated as number of participants who complete 8-week measures / number of participants enrolled into the study x 100. Data completion rates will be calculated as the number of complete datasets for each outcome measure / number of participants enrolled ×100.

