## Abstract

The workplace is a major contributor to excessive sitting in office workers. There are a wide array of adverse effects of high volumes of sitting time, including an increased risk of type 2 diabetes and depression. Active workstations can be used in effective interventions to decrease workplace sitting. However, there are a lack of interventions that have been developed using a systematic process that is informed by participant needs and a framework for identifying the most appropriate content for the intervention. Applying these methods could increase adherence and potential effectiveness of the intervention. Therefore, the purpose of this pilot study is to examine the feasibility, acceptability, and efficacy of a tailored workplace intervention to reduce and break up sitting in office workers that has been developed using the Behavior Change Wheel and the APEASE (Acceptability, Practicability, Effectiveness/cost-effectiveness, Affordability, Safety/side-effects, Equity) criteria. This article reports the protocol for this study that is currently ongoing. Participants will be cluster-randomized (by offices) to control and intervention groups. The evaluation of the intervention includes determining feasibility by assessing participant recruitment, retention and data completion rates. Adherence to the intervention will be assessed based on daily sitting and standing time relative to guidelines provided to participants as part of the intervention. Outcome measures also include productivity measured using Ecological Momentary Assessment, absenteeism, presenteeism, cardiometabolic risk markers, and wellbeing. The findings of this study will inform the effective design and implementation of interventions for reducing and breaking up sitting in office workers.

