### Participant Recruitment

Management approval will be sought and obtained for the recruitment of the employees, changes to the workplace environment, and for study testing and communications to take place during work time. The project will be advertised to staff as part of a workplace wellbeing programme via internal mail, staff meetings, information fliers in offices and other strategic places within the participating organizations.

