### Eligibility Criteria

Participants will be full-time desk-based office employees between the ages of 18 and 60 years employed in any job type and from any ethnic background. Individuals will be excluded from the study if they are pregnant, have a history of musculoskeletal complaints, non-ambulatory, or have a planned holiday that would mean they would not be at work for more than 2 weeks during the 8-week intervention period.

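### The eligibility rate is defined upside down (screened over eligible), so it can never fall below 100%; the response rate may also be overstated, depending on who is invited

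*Protocol article*

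**What the plan says.** The Feasibility section of the protocol article defines four rates. Two concern recruitment:

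- Response rate: "recruitment response rate (percentage of people who express interest in participating in the study / number of invitations sent out to individuals x 100".
- Eligibility rate: "eligibility rate (percentage of individuals who are screened / number of individuals eligible to take part x 100".

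The other two are retention and data completion. For retention, "Retention rate will be calculated as number of participants who complete 8-week measures / number of participants enrolled into the study x 100". Data completion likewise divides complete datasets by participants enrolled.

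Two other sections bear on these definitions. Under Participant Recruitment, staff are to be told of the project "via internal mail, staff meetings, information fliers in offices and other strategic places within the participating organizations". Under Eligibility Criteria, "Individuals will be excluded from the study if they are pregnant, have a history of musculoskeletal complaints, non-ambulatory, or have a planned holiday" of a stated length, so some of the people screened can be turned away.

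The Abstract describes the evaluation as including "determining feasibility by assessing participant recruitment, retention and data completion rates".

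**The concern.** An eligibility rate is the share of screened people who qualify. The printed formula divides the other way. Anyone who follows it will report a figure that cannot be a proportion and that looks better the worse eligibility is. Both recruitment formulas also open with 'percentage of', then divide and multiply by 100, where a count is meant.

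The response rate raises a separate and weaker question. Its numerator is everyone who expresses interest. Its denominator is invitations sent to individuals. Recruitment also runs through meetings and fliers, so the two may not describe the same people.

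Feasibility is one of the pilot's stated aims, and the Discussion says the findings can inform a fully powered trial. These are the only two recruitment measures that the section defines, so they should be readable as printed.

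**Working it through.** The article gives no counts of people invited, interested, screened or eligible, and sets no feasibility target. There is therefore no stated figure to reproduce. All counts below are assumed for illustration; the algebra does not depend on them.

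**Eligibility rate.** Let S be the number screened and E the number found eligible, with E ≤ S.

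- As written: S / E x 100. Since E ≤ S, this is at least 100%. It equals 100% only if nobody is screened out.
- As the name implies: E / S x 100, which lies between 0% and 100%.
- If the true rate is p (as a proportion), the written formula reports 100 / p.

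| True eligibility | Reported as written |
|---|---|
| 90% | 100 / 0.9 = 111.1% |
| 80% | 100 / 0.8 = 125% |
| 60% | 100 / 0.6 = 166.7% |
| 50% | 100 / 0.5 = 200% |

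In counts, taking 44 eligible people:

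| Screened | As written | Right way round |
|---|---|---|
| 50 | 50 / 44 = 113.6% | 44 / 50 = 88.0% |
| 60 | 60 / 44 = 136.4% | 44 / 60 = 73.3% |
| 80 | 80 / 44 = 181.8% | 44 / 80 = 55.0% |

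**Comparison within the section.** Retention is completers over enrolled, and data completion is complete datasets over enrolled. Both are part over whole. The eligibility rate alone is whole over part, which suggests a transposition.

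**Response rate.** Assume 60 people express interest, 40 of them through an individual invitation and 20 through other channels only, with 300 staff reached in all.

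| Invitations | As written | Invited responders only | All interested / all reached |
|---|---|---|---|
| 200 | 60 / 200 = 30% | 40 / 200 = 20% | 60 / 300 = 20% |
| 100 | 60 / 100 = 60% | 40 / 100 = 40% | 60 / 300 = 20% |
| 50 | 60 / 50 = 120% | 40 / 50 = 80% | 60 / 300 = 20% |

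Now assume instead that 200 invitations reach all 200 targeted staff. Everyone who saw a flier or attended a meeting is then already in the denominator. The written rate is 60 / 200 = 30% and needs no correction. The error thus runs from zero to a rate above 100%, and the article does not say where in that range the trial falls.

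**The case against.** **On the eligibility rate.** One could read the denominator as a wider pool of staff who would qualify, which would make the ratio a measure of how much of that pool was screened. The label *eligibility rate* makes that reading weak. Nor does the brevity of a journal article explain the formula: it is stated in full, and it is the wrong way up.

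The better objection is about consequence, and it stands. A result above 100% shows itself to be wrong. The reciprocal restores the intended figure, or it can be recomputed from the counts. No data are lost and nothing in the conduct of the trial changes.

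**On the response rate.** A reader might infer that this rate, too, would be wrong, because people recruited by flier or meeting enter the numerator only. The article does not support that. Internal mail is among the listed channels, and if it goes to all targeted staff the formula is sound. How invitations are counted is also detail that an article may leave to the full protocol. What remains is that nothing limits the numerator to invited people, so the rate may be overstated.

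**On importance.** A reader might also infer that these rates determine recruitment numbers for the full trial. The article says only, in general terms, that the findings can inform one. Its Sample Size section gives the main purpose of pilot studies as estimating a standard deviation, and the Abstract's list of feasibility rates does not name eligibility separately.

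**Conclusion.** The eligibility formula is wrong as printed. This follows from the text alone and rests on no assumption beyond the eligible being drawn from the screened. The reported value would be the reciprocal of the true rate: never below 100%, and higher as eligibility falls. Writing 'percentage of' for 'number of' in both recruitment formulas is a slip with no likely numerical effect.

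The response-rate point is conditional. The rate may be overstated if some interested people were reached only through fliers or meetings. The error is zero if invitations cover all targeted staff, and its size cannot be fixed from the article.

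Severity is minor. No progression threshold, sample size or primary analysis uses either rate.

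**What to change.** 1. Define the eligibility rate as number of individuals eligible / number of individuals screened x 100.
2. In both recruitment formulas, replace 'percentage of' with 'number of'.
3. Match the two parts of the response rate in one of two ways:
   - limit the numerator to people who received an individual invitation; or
   - use all staff approached as the denominator. This must cover every recruitment channel, including the places outside offices where fliers are put, or the mismatch returns.

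   If invitations go to all targeted staff, a sentence saying so is enough.

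Items 1 and 2 cost only wording. Item 3 costs wording under the first option, plus a record of how each interested person was reached. Under the second it needs a staff headcount from each organisation. An office-level recruitment rate might be useful to a later trial, but it would be an added outcome and this correction does not need it.
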